## Abstract

**Background:**

The use of spirometry for early detection of chronic obstructive pulmonary disease (COPD) is still an issue of debate, particularly because of a lack of convincing evidence that spirometry has an added positive effect on smoking cessation. We hypothesise that early detection of COPD and confrontation with spirometry for smoking cessation may be effective when applying an approach we have termed "confrontational counselling"; a patient-centred approach which involves specific communication skills and elements of cognitive therapy. An important aspect is to confront the smoker with his/her airflow limitation during the counselling sessions. The primary objective of this study is to test the efficacy of confrontational counselling in comparison to regular health education and promotion for smoking cessation delivered by specialized respiratory nurses in current smokers with previously undiagnosed mild to moderate airflow limitation.

**Methods/Design:**

The study design is a randomized controlled trial comparing confrontational counselling delivered by a respiratory nurse combined with nortriptyline for smoking cessation (experimental group), health education and promotion delivered by a respiratory nurse combined with nortriptyline for smoking cessation (control group 1), and "care as usual" delivered by the GP (control group 2). Early detection of smokers with mild to moderate airflow limitation is achieved by means of a telephone interview in combination with spirometry. Due to a comparable baseline risk of airflow limitation and motivation to quit smoking, and because of the standardization of number, duration, and scheduling of counselling sessions between the experimental group and control group 1, the study enables to assess the "net" effect of confrontational counselling. The study has been ethically approved and registered.

**Discussion:**

Ethical as well as methodological considerations of the study are discussed in this protocol. A significant and relevant effect of confrontational counselling would provide an argument in favour of early detection of current smokers with airflow limitation. Successful treatment of tobacco dependence in respiratory patients requires repeated intensive interventions. The results of this study may also show that respiratory nurses are able to deliver this treatment and that intensive smoking cessation counselling is more feasible.

**Trial registration::**

Netherlands Trial Register (ISRCTN 64481813).

## Background

Chronic obstructive pulmonary disease (COPD) is a preventable and treatable disease which is characterized by airflow limitation that is not fully reversible [1]. Spirometry is the gold standard for the diagnosis and assessment of the disease [1]. COPD is currently the fifth leading cause of death worldwide [2], and projections for 2020 indicate further increase in global mortality, placing COPD on the third position of lethal diseases [3]. Cigarette smoking is by far the most important risk factor for COPD, and smoking cessation is the single most effective way to reduce the risk of developing COPD and to affect the outcome in patients at all stages of the disease [4,5].

Underdiagnosis of COPD is a worldwide problem [6]. Most patients present to their doctor for various other reasons but often have respiratory symptoms, and in those who do present with respiratory symptoms, COPD is not always suspected nor diagnosed [7]. Because of the irreversible and progressive nature of the disease, early intervention is important. However, the use of spirometry for early detection of COPD is still an issue of debate [8-10]. The most important counterargument is that there is no convincing evidence that spirometry has an added positive effect on smoking cessation [11-13].

### Why use spirometry for smoking cessation?

In theory, spirometry might be useful as a motivational tool for smoking cessation in smokers who are at risk of developing (or have) COPD. While most smokers acknowledge that smoking is dangerous, many trivialize their own perceived risk of the disease, or deny or avoid information about the dangers of smoking in order to reduce cognitive dissonance [14-18]. One might therefore expect that confronting smokers with an objectively (by spirometry) identified negative consequence of smoking (airflow limitation) positively affects the outcome of their quit attempt. This idea was already proposed in the 1960's by Peters and Ferris who argued that assessing the negative effects of smoking on lung function "might serve as a lever to influence the young adult to reduce his smoking habits" [19]. Since then, various studies have been performed to study the efficacy of spirometry for smoking cessation. The results, however, are inconclusive as shown in a the systematic review by Wilt et al. on spirometry as a motivational tool for smoking cessation [11,12]. Also, previous studies have one or more important methodological limitations such as unstandardized counselling intensity, incomparable or uncontrolled use of pharmacological aids for smoking cessation between experimental and control group, and different (or unclear) baseline levels of lung function and motivation to quit smoking. More well-designed research is needed to assess the efficacy of spirometry for smoking cessation.

### Hypothesis and research questions

We hypothesise that early detection of COPD and confrontation with spirometry for smoking cessation may be effective if the following approach we have termed "confrontational counselling" is applied [20]. Confronting patients with COPD is not an isolated approach but should be integrated into state-of-the-art smoking cessation treatment. Confrontational counselling should consist of several counselling sessions on an individual, face-to-face level, under supervision of a trained smoking cessation specialist, and in combination with evidence-based pharmacological treatment for smoking cessation.

Our primary research question is: what is the efficacy of confrontational counselling in comparison to regular health education and promotion for smoking cessation delivered by specialized respiratory nurses in current smokers with previously undiagnosed mild to moderate airflow limitation (i.e. GOLD [1] stage 1 and 2 COPD) with regard to prolonged abstinence from smoking during a period of 12 months?

In this group of smokers with previously undiagnosed mild to moderate airflow limitation we want to address the following secondary research questions:

1. Which baseline characteristics are predictors of outcome (i.e. 12-month prolonged abstinence from smoking)?

2. What are the effects of early detection of airflow limitation and smoking cessation on lung function, perceived specific health-related complaints, quality of life, and mental health after 12 months follow-up?

3. What is the cost-effectiveness and cost-utility of early detection in combination with confrontational counselling delivered by respiratory nurses?

4. What are the effects of labelling of disease (COPD) on self-efficacy, perceived health status, quality of life and mental health?

5. What are the ethical considerations of early detection of airflow limitation and subsequent confrontational counselling for smoking cessation?

## Methods/Design

### Study design

In short, the design of this study is a randomized controlled trial comparing confrontational counselling delivered by a respiratory nurse (RN) combined with nortriptyline for smoking cessation (experimental group), health education and promotion delivered by a RN combined with nortriptyline for smoking cessation (control group 1), and "care as usual" delivered by the GP (control group 2). Early detection of smokers with mild to moderate airflow limitation is achieved by means of a telephone interview in combination with spirometry. For an overview of the study design see figure 1.

**Figure 1 F1:**
[figure not shown]
**Design**. FC = face-to-face counselling session; TC = telephone counselling session; TQD = target quit date; RN = respiratory nurse; GP = general practitioner.

The efficacy of smoking cessation interventions in clinical studies depends on the characteristics of the study population, the intensity of behavioural support, and the use of pharmacological aids for smoking cessation [21]. In order to isolate the effect of confrontational counselling on smoking cessation, other factors that are associated with the outcome must be standardized between the comparison groups. All participants of this trial have previously undetected mild to moderate airflow limitation. Participants from both the experimental group and control group 1 receive an equally intensive counselling (in terms of number, duration, and scheduling of counselling visits) and dosage of nortriptyline for smoking cessation. Another reason for using an active control is that it would not be ethically sound to withhold smokers with airflow limitation from smoking cessation treatment.

### Sample size calculation

The primary research question aims at a contrast in efficacy between the experimental group (confrontational counselling) and control group 1 (health education and promotion). Therefore, the calculation of the sample size is based on the identification of a difference in proportion of prolonged abstinence after 12 months between these two groups. We estimated the relevant difference in proportion to be 15%: 35% quitters in the experimental group versus 20% quitters in control group 1. When putting the risk of a type I-error at 5% and the risk of a type II-error at 20%, 136 participants per group are needed at onset to detect a difference in proportions of 15%. Considering 10% lost to follow-up, 150 participants per group are needed in the experimental group and control group 1 (136 × 0.9^-1^). We expect a larger difference between the experimental group (35%) and control group 2 (8% [22]). Therefore, less participants are needed in control group 2. We used a formula for the calculation of sample sizes of unequal groups and set the ratio between the experimental group and control group 2 at 3:1. This resulted in a minimum of 32 participants in control group 2 (taking into account 10% lost to follow-up).

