### Randomization and planning procedure

All eligible subjects with previously undetected mild to moderate airflow limitation are contacted by telephone a few days after baseline spirometry to be randomised to one of the three intervention groups (apart from those candidates who changed their mind and who are no longer willing to participate in the study). Also at this moment, the results of spirometry are not discussed. The database of the trial incorporates a randomization system of seven participants per block, allowing an unequal group allocation of 3 : 3 : 1; experimental group : control group 1 : control group 2. When eligible subjects are contacted by telephone, the RA randomises the subject by pressing a button on the computer screen. The database then randomly allocates the subject. Neither the primary researcher nor any other person involved in the study can predict or influence which treatment group the next participant will be allocated to.

After randomization, all treatment and follow-up visits are planned for the whole study period. A schedule with all visits is sent to the participant. At the same time, the GP of each participant is sent a letter informing the GP that the participant is taking part in the study.

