### Data analysis

The primary outcome measure is prolonged abstinence from smoking during a period of 12 months after the TQD. Prolonged abstinence is defined as follows: abstinent from smoking at all three follow-up visits; at day 50 (approximately 5 weeks after the TQD), day 197 (after six months), and day 379 (after 12 months). Participants are allowed to miss the second follow-up visit (day 197) if they have been abstinent from smoking at the first (day 50) and the last follow-up visit (day 379; interpolation). A participant is defined as abstinent from smoking at a follow-up visit if both of the following two conditions are met:

1. urine cotinine level < 50 ng/mL [37] and

2. self-reported quitter, not having smoked a single cigarette since stopped smoking.

All randomized subjects will be included in the analysis and subjects not showing up at the follow-up visit or with a missing value on one of the two above measures are regarded as smokers (intention-to-treat analysis). Statistical difference in primary outcome will be analyses using Chi-square tests.

The secondary research questions will be analysed as follows (see the last paragraph of the introduction for an overview of all secondary research questions).

1. Baseline predictors of outcome will be analysed by regressing the primary outcome measure (12-month prolonged abstinence) on candidate predictors measured at baseline (such as age, sex, airflow limitation, previous quit attempts, or nicotine dependence) in a multivariate logistic regression model, controlling for treatment group.

2. The health effects of smoking cessation will be analysed by regressing measures of lung function, perceived specific health-related complaints, quality of life, and mental health on abstinence at each follow-up visit using linear regression models.

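### The 10% loss allowance does not match an analysis that counts lost participants as smokers, and 136 × 0.9^-1 is 151.1, not 150; power at 150 per group is about 83.5% or 78%, depending on an unstated definition of the assumed rates

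*Protocol article*

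**What the plan says.** Under Sample size calculation, the Protocol article bases the number on the primary contrast between the experimental group and control group 1: "calculation of the sample size is based on the identification of a difference in proportion of prolonged abstinence after 12 months between these two groups". The assumed rates are "35% quitters in the experimental group versus 20% quitters in control group 1", with 5% type I and 20% type II error, which gives 136 per group. The paragraph then adds an allowance for loss: "Considering 10% lost to follow-up, 150 participants per group are needed in the experimental group and control group 1", with the expression 136 × 0.9^-1 printed beside it.

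Under Data analysis, the primary analysis has no exclusions for loss. It begins "All randomized subjects will be included in the analysis and subjects not showing up at the follow-up visit", and the rule is that "subjects not showing up at the follow-up visit or with a missing value on one of the two above measures are regarded as smokers". There is one relaxation: a missed day 197 visit does not count against a participant who is abstinent at day 50 and day 379. The test is a chi-square test.

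**The concern.** Dividing by one minus the loss fraction keeps the analysed number at its target when lost participants drop out of the denominator. Here they stay in it as failures. Loss then has no effect on the number analysed. It pulls both abstinence rates down and narrows the difference between them, and dividing by 0.9 does not correct for that.

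Whether any allowance is needed depends on what 35% and 20% describe. If they are rates of the outcome as defined under Data analysis, failures through loss are already in them and no inflation is called for. If they are rates among participants who are followed up, the allowance has to be computed from the diluted rates. The sample size paragraph does not say which. The printed product also does not equal the number given. At stake is whether a reader can tell what difference the sole primary comparison is powered to detect, and with what power.

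**Working it through.** **Inputs.** From Sample size calculation: 35% and 20%, type I error 5%, type II error 20%, 136 before and 150 after a 10% loss allowance. From Randomization and planning procedure: 3:3:1 allocation, so 1:1 for this contrast. From Data analysis: all randomised analysed, missing counted as smoking, chi-square test. Sidedness is not stated. I take two-sided, which fits a chi-square test and the figure of 136 (a one-sided calculation gives 109).

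**1. The plan's 136.** The unpooled formula is n = (z₀.₉₇₅ + z₀.₈₀)² × [p₁(1−p₁) + p₂(1−p₂)] / (p₁−p₂)².

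(1.96 + 0.8416)² × (0.35×0.65 + 0.20×0.80) / 0.15² = 7.849 × 0.3875 / 0.0225 = 135.2, rounded up to 136. This reproduces the stated figure. The version with pooled variance under the null gives 137.9, so 138.

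**2. The inflation as printed.** 136 / 0.9 = 151.1, or 152 rounded up. The stated 150 is close to 136 × 1.1 = 149.6. On the plan's own logic, 150 × 0.9 = 135 would remain. Power for 35% versus 20% with 135 per group is 79.6% exact (79.1% pooled, 79.9% unpooled), so the slip costs less than 1 point.

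**3. Power at 150 per group under the stated analysis.**

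- *Rates among all randomised, missing counted as smoking.* The analysed rates are 35% and 20%. Unpooled: 0.15 / √(0.3875/150) = 2.951; 2.951 − 1.960 = 0.991; Φ(0.991) = 83.9%. Pooled: 83.2%. Exact binomial enumeration of the uncorrected chi-square test: 83.5%. With no inflation, 136 per group already gives 80.0% exact.
- *Rates among those followed up.* With 10% loss in each arm and every loss a failure, the analysed rates are 0.9 × 35% = 31.5% and 0.9 × 20% = 18%, a difference of 13.5 points. The variance sum is 0.315×0.685 + 0.18×0.82 = 0.3634. Unpooled: 0.135 / √(0.3634/150) = 2.743; 2.743 − 1.960 = 0.783; Φ(0.783) = 78.3%. Pooled: 77.6%. Exact: 78.0%. For 80% power, n = 7.849 × 0.3634 / 0.135² = 156.5, so 157 (unpooled), or 160 (pooled).

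**4. Correcting the division alone.** At 151 per group, exact power is 83.8% on the all-randomised definition and 78.4% on the followed-up definition. The product slip therefore does not explain the gap between the two.

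**5. Dependence on the test.** These figures are for the chi-square test without continuity correction, the version consistent with 136 (the continuity-corrected formula gives 151 before any loss allowance). With Yates' correction, which the protocol does not mention, exact power at 150 would be 79.9% and 73.7% respectively.

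**The case against.** A reader might infer that 150 per group misses 80% power on the plan's own assumptions. The documents do not support that. The rates are introduced as proportions with prolonged abstinence, and Data analysis defines that outcome with the lost counted as smokers. Read in that way, 150 per group exceeds 80% and the allowance is merely conservative. A shortfall needs the premise that 35% and 20% apply only to those followed up. The presence of a loss allowance hints at that premise, but nothing states it. This part of the objection stands.

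Even on the unfavourable definition the shortfall is about 2 points. It assumes 10% loss in both arms with every loss a failure, and the relaxation for a missed day 197 visit would soften the dilution somewhat. The assumed rates are themselves estimates, and no design decision turns on 78% versus 80%. This also stands and limits the weight of the point.

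On the arithmetic, the unrounded requirement gives 135.2 / 0.9 = 150.2, so 150 could come from carrying the unrounded value and rounding to the nearest whole number. That may explain the figure, but the expression printed is 136 × 0.9^-1, and it does not equal 150.

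None of this answers the mismatch itself. The allowance treats lost participants as leaving the analysis, and the analysis rule keeps them in. Both statements are in the article, so this is not a detail left to a fuller document.

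**Conclusion.** The loss allowance and the primary analysis rule are inconsistent, and the printed product is wrong by one to two participants. Under the stated analysis, power at 150 per group is about 83.5% if 35% and 20% are all-randomised rates and about 78% if they are rates among those followed up. The stated 80% is neither.

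This rests on a two-sided 5% uncorrected chi-square test and 1:1 allocation. The lower figure also rests on 10% loss in each arm with every loss counted as smoking. The point concerns a power statement that does not follow from its own premises. It does not show that the trial is too small.

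**What to change.** State in the sample size paragraph whether 35% and 20% are rates among all randomised participants with missing counted as smoking. The answer should reflect what was meant when the rates were chosen.

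- If they are, drop the 10% inflation for this comparison and restate power at 150 per group as about 83-84%.
- If they are rates among those followed up, restate power at 150 per group as about 78% for 31.5% versus 18%, and give the loss assumption behind it.

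In either case, correct the product: 136 × 0.9^-1 is 151.1. The cost is one clarifying clause, one restated power figure and one corrected number. Design, analysis and enrolment do not change.

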### Preparation of the trial

In preparation of the trial, all GPs in Dutch and Belgian Limburg (the area surrounding the city of Maastricht) have been informed about the study. We have prepared an office for the screening, counselling, and follow-up visits of participants at Medical Centre Annadal, Maastricht. We have built a relational database for the control of all study events and the collection of data. This is very important because of the complexity of the study.

### Recruitment of participants

Subjects are recruited in the general population (through advertisements in local newspapers, flyers, posters, and mailings to households) and in primary care practices (during consultations and through posters and personalized mailings) in Dutch and Belgian Limburg. The text in the advertisements, on flyers, and on posters explains that Maastricht University is performing a study on smoking cessation treatment in which individual counselling is combined with medication for smoking cessation. Current smokers aged 35 to 70 years, who are motivated to quit smoking, are asked to contact us by telephone or by e-mail. We also refer to a website with information about this study. No information about the target condition we are looking for (airflow limitation) is given to participants during recruitment.

### In- and exclusion criteria and process of eligibility screening

Eligibility is screened in two steps; during an initial telephone interview followed by spirometry. The following inclusion criteria are checked during the telephone interview: smoking history of 10 or more pack years; being motivated to stop smoking; being competent to read and speak Dutch; and reporting a respiratory symptom, defined as an affirmative answer to at least one of the following three questions: "Do you cough regularly?", "Do you cough up phlegm (sputum) when you don't have a cold?" or "Have you been shorter of breath lately?". Exclusion criteria are: evidence of a prior respiratory diagnosis, defined by an affirmative answer to the question "Do you have COPD, chronic bronchitis, asthma or asthmatic bronchitis?". Participants are also not allowed to have undergone a lung function test (spirometry) during the preceding 12 months. One or more contraindications for using the smoking cessation medication (nortriptyline) are also reasons for exclusion, among others the current use of anti-depressants. Nortriptyline is a tricyclic anti-depressant which should not be used for smoking cessation in conjunction with another anti-depressant. After the end of the telephone interview, an appointment for spirometry at Medical Centre Annadal is scheduled. Subjects are eligible for participation who have airflow limitation defined as post-bd. FEV_1_/FVC < 70% in combination with post-bd. FEV_1_≥ 50% of predicted value; i.e. mild (GOLD 1) or moderate (GOLD 2) airflow limitation, according to the international GOLD guideline [1]. The results of spirometry are not discussed during or directly after spirometry.

Subjects with severe airflow limitation (post-bd. FEV_1_/FVC < 70% in combination with post-bd. FEV_1 _< 50% of predicted value) are excluded from participation and advised to contact their GP or a lung physician for further evaluation. Subjects without airflow obstruction (post-bd. FEV_1_/FVC ≥ 70%) are also excluded. These smokers are told that despite their normal lung function, they still are at risk of getting other smoking related diseases which are not measured by spirometry, such as cancer or cardiovascular disease. They are strongly recommended to give up smoking. Both groups of excluded smokers get the advice to stop smoking and receive a box with information material about all existing therapies for smoking cessation from the Dutch foundation for a smoke free future (STIVORO).

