### Spirometry

Spirometry is performed by two qualified research assistants under permanent supervision of a pulmonologist (GW) according to the criteria of the American Thoracic Society (ATS)/European Respiratory Society (ERS) task force for standardization of lung function testing [23,24] using a Vitalograph^® ^2120 (Vitalograph Ltd, Buckingham, England). After a minimum of three acceptable and reproducible FVC manoeuvres, a bronchodilator (500 μg terbutaline) is administered to the subject in preparation for the reversibility test. After 15 minutes, another series of three FVC manoeuvres is performed. All spirometric test results are independently validated by a pulmonologist (GW) and by a specialised lung function laboratory assistant who was not involved in the trial. In case of initial disagreement, consensus is obtained during re-examination.

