### Informed consent procedure

Written information about the study is sent to the candidate participant after the telephone interview, along with the informed consent form. The candidate has at least one week time for reflection before spirometry and can contact the researcher or the research assistant (RA) for further information at any time. The informed consent form is signed by the participant in presence of the RA during the visit for baseline spirometry.

The participant information letter gives information about the existence of two intervention groups only. It says that in one group participants receive "care as usual" by their own GP (this is control group 2) and in the other group participants receive treatment from a trained RN. The latter group is in fact a combination of the experimental group (confrontational counselling by RN + nortriptyline) and control group 1 (health education and promotion by RN + nortriptyline). These two groups are identical with regard to the number and duration of counselling sessions and the use of nortriptyline, but differ only concerning the content and style of the behavioural support: confrontational counselling versus health education and promotion. Just this difference in content must not explicitly be mentioned in the participant information letter in order to safeguard the internal validity of the study. We would jeopardize the idea behind early detection of patients with airflow obstruction by means of spirometry if we would speak about "confrontational counselling" or mention the target condition (airflow limitation). Participants must not know that we use results from spirometry as part of one intervention. The design we use is adapted from Zelen's design [25,26] which may be particularly useful when evaluating the full unbiased impact of screening interventions [27].

At the end of the study, after the 12-month follow-up visit, all participants will indeed be fully informed about the real nature of the study. All participants and their corresponding GPs will be informed about the result of the spirometry. If a GP needs the results of spirometry for the regular care of his/her patient before the end of the study, the required information will be provided. This procedure is approved by the medical ethics committee of Maastricht University and Maastricht University Hospital.

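### Screened smokers with a post-bronchodilator FEV1/FVC of 70% or more are all told their lung function is normal, which that ratio alone does not show

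*Protocol article*

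**What the plan says.** The section on in- and exclusion criteria and eligibility screening creates two groups that are excluded after spirometry.

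- **Severe airflow limitation** (post-bronchodilator FEV1/FVC below 70% and FEV1 below 50% of predicted). These subjects "are excluded from participation and advised to contact their GP or a lung physician for further evaluation".
- **No airflow obstruction** (post-bronchodilator FEV1/FVC of 70% or more). The only condition is the ratio; nothing is required of FEV1 or FVC as a percentage of predicted, or of the values before bronchodilator. The message is: "These smokers are told that despite their normal lung function, they still are at risk of getting other smoking related diseases". The sentence goes on to mention cancer and cardiovascular disease, and quitting is strongly recommended.

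Both groups get stop-smoking advice and a box of information material. Advice to see a doctor is stated for the severe group only.

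The Spirometry section shows what is recorded and who looks at it. After the first series of manoeuvres a bronchodilator "is administered to the subject in preparation for the reversibility test", so values before and after are both available. "Spirometry is performed by two qualified research assistants under permanent supervision of a pulmonologist", and "All spirometric test results are independently validated by a pulmonologist" and by a laboratory assistant from outside the trial.

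**The concern.** The article treats absence of post-bronchodilator obstruction as if it were normal lung function, and makes that the message to everyone in the group. The two are not the same. A ratio stays the same when both its parts fall in proportion, and a post-bronchodilator ratio cannot show obstruction that the drug has just relieved.

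The people concerned are not a random sample of healthy smokers. To reach spirometry they must report at least one of three respiratory symptoms and have 10 or more pack years. They must also deny a diagnosis of COPD, chronic bronchitis, asthma or asthmatic bronchitis. For such a person, being told that lung function is normal when it is not is inaccurate information from a clinical team, and it may make follow-up of the symptom less likely. What is at stake is the accuracy of information and a small safety matter for screened subjects, not the trial's inference.

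**Working it through.** The article gives no figure on this point to reproduce. The check is whether a post-bronchodilator ratio of 70% or more can coexist with abnormal values, and how extreme those values must be. The predicted ratios and volumes below are assumptions, because the article gives none.

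**1. Proportional loss.** Assume predicted FEV1 3.2 L and FVC 4.0 L. With both at 100% of predicted the ratio is 3.2/4.0 = 0.80. With both at 50% it is 1.6/2.0 = 0.80. Both subjects fall in the group told normal.

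**2. FEV1 below the plan's own 50% cut.** FEV1 (% predicted) = FVC (% predicted) × measured ratio / predicted ratio. FEV1 below 50% therefore needs FVC (% predicted) below 50 × predicted ratio / measured ratio.

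| Measured ratio | Predicted ratio 0.75 | Predicted ratio 0.82 |
|---|---|---|
| 0.70 | 50 × 0.75/0.70 = 53.6% | 50 × 0.82/0.70 = 58.6% |
| 0.80 | 50 × 0.75/0.80 = 46.9% | 50 × 0.82/0.80 = 51.3% |

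FVC must be below about 47% to 59% of predicted, depending on the ratios. This is possible but probably rare.

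An example is a measured ratio of 0.74 with FEV1 at 45% of predicted, which implies FVC between 45 × 0.75/0.74 = 45.6% and 45 × 0.82/0.74 = 49.9% of predicted. Under the stated rule this subject is told normal. The same FEV1 with a ratio of 0.69 would put the subject in the severe group, with advice to see a doctor.

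**3. Obstruction reversed by the bronchodilator.** Hold FVC at an assumed 4.0 L and let the ratio cross 70%.

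| Ratio before → after | FEV1 before → after | Rise in FEV1 |
|---|---|---|
| 0.60 → 0.72 | 2.40 → 2.88 L | 0.48 L, 20.0% |
| 0.68 → 0.71 | 2.72 → 2.84 L | 0.12 L, 4.4% |
| 0.69 → 0.70 | 2.76 → 2.80 L | 0.04 L, 1.4% |

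The first row is a marked response in a symptomatic smoker without known asthma, and normal is the wrong word for it. The last row is trivial. A crossing of 70% does not by itself separate the two; the size of the response and clinical judgement do.

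**4. Stated routes by which an abnormal value could still reach a doctor.**

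- The pulmonologist's validation has no stated action attached for values outside the eligibility rule.
- End-of-study disclosure covers participants after the 12-month visit, which screened-out smokers do not have.
- The Informed consent section offers results on request: "If a GP needs the results of spirometry for the regular care of his/her patient before the end of the study". This is not expressly closed to excluded subjects, but it depends on the GP asking.
- GPs in the region "have been informed about the study" in general terms. The letter about an individual comes after randomisation: "the GP of each participant is sent a letter informing the GP that the participant is taking part in the study".

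**The case against.** The strongest reply has four parts.

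*The article is a summary.* Handling of incidental findings in people screened out, and the exact script, are things a journal article commonly leaves to the full protocol. This stands for the missing referral step, which is the weaker half of the point. It does not dispose of the stated message, which ties normal lung function to a definition based on the ratio alone.

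*A pulmonologist supervises and validates every test.* Such cases may well be caught in practice. A reader might infer that the plan leaves abnormal results unattended or bars referral; the article says neither. Equally, it attaches no action to the validation.

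*The sentence is meant to prevent false reassurance.* It warns of other diseases and urges quitting. That is true and lessens the harm, but those warnings concern diseases that spirometry does not measure, and they leave the statement about the lungs uncorrected. That the word normal would discourage follow-up is plausible but not shown by the document.

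*The plan defines airflow limitation after bronchodilator, following GOLD.* A reader might infer that every subject with a ratio below 70% before bronchodilator should be referred. The article does not support that: it would send a 0.69 to 0.70 crossing to a doctor even where the pulmonologist sees nothing wrong.

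It is also tempting to say that any abnormal value would be new to the subject and the GP. The screening question asks only about the named obstructive and bronchitic diagnoses, and spirometry is barred only for the preceding 12 months, so a known non-obstructive cause or an older abnormal result is possible.

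**Conclusion.** The point holds as a minor one, worth considering. As stated, the rule tells a whole group that their lung function is normal on a criterion that shows only no obstruction after bronchodilator. Followed literally, it misinforms a symptomatic smoker with low FEV1 or FVC, or with clearly reversible obstruction. That conclusion follows from the definition and does not depend on the assumed volumes.

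The number affected is unknown. The Discussion says only that many smokers must be screened. The low-FEV1 case is probably rare under the assumed predicted ratios of 0.75 to 0.82; the reversible cases range from trivial to marked.

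A reader might infer some bias in the trial result. There is none from this source: the people concerned are never randomised, and allocation, endpoint, sample size and primary analysis are unaffected. Confidence is moderate, because a fuller script may exist outside the article.

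**What to change.** Change the message for the group with a ratio of 70% or more as follows.

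1. By default, say in neutral wording that the test shows no sign of a fixed problem, without naming airflow limitation.
2. Use the word normal only when the pulmonologist who already validates every test judges the values normal.
3. If post-bronchodilator FEV1 is below the plan's own 50% of predicted cut, or the pulmonologist judges FEV1, FVC or the reversibility result abnormal, give instead the advice already used for the severe group: contact the GP or a lung physician.
4. Set no automatic trigger on the pre-bronchodilator ratio.

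Keep the warning about other smoking-related diseases and the advice to quit. If this is already practice, one sentence in the article is enough.

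The values are already recorded and already reviewed, so no test or staff member is added. The cost is some extra GP contacts, whose number cannot be computed from the article. Since the severe group already receives the same advice, neutral wording should add little risk of revealing the target condition during recruitment.
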